### 9.4.2.2 Definition of a Serious Adverse Event

A serious adverse event (SAE) is defined as any untoward medical occurrence that, at any dose:

1. Results in death
2. Is life-threatening
3. Requires hospitalization or prolongation of existing hospitalization
4. Results in disability/incapacity
5. Is a congenital anomaly/birth defect
6. Is otherwise considered as medically important.

### 9.4.2.3 Recording of AEs and SAEs

When an AE/SAE occurs, it is the responsibility of the investigator to review all documentation (e.g. hospital progress notes, laboratory, and diagnostics reports) relative to the event. The investigator will then record all relevant information regarding an AE or SAE on the eCRF. Any AEs or SAEs occurring during the study must be documented in the subject's medical records and on the appropriate page of the eCRF. Each AE or SAE is to be recorded individually. All AEs which occur

[figure not shown]

during the course of the study should be recorded in the eCRF. Information on the AE must be recorded on a specific AE form (appendix 5).

#### *9.4.2.4 Evaluating AEs and SAEs*

##### *9.4.2.4.1 Assessment of intensity*

The investigator will make an assessment of intensity of each AE and SAE reported. In this protocol, the intensity of AEs and SAEs will be graded on a scale of 1 to 5 according the National Cancer Institute (NCI) Common Toxicity Criteria for Adverse Events (CTCAE) Version 5 and are available at <https://evs.nci.nih.gov/ftp1/CTCAE/About.html>.

For SAEs, the maximum intensity (or grade) will be reported in the eCRF. For non-serious AEs, each change in intensity (or grade) will be reported in the eCRF.

##### *9.4.2.4.2 Assessment of causality*

The investigator is obliged to assess the relationship between the study medical product and the occurrence of each AE/SAE and provide the assessment of causality as per instructions on the SAE form in the Investigators File.

##### *9.4.2.4.3 Follow-Up of AEs and SAEs*

After the initial AE/SAE report, the investigator is required to proactively follow each subject and provide further information on the subject's condition by any supplemental investigations as may be indicated to elucidate the nature and/or causality of the AE or SAE. AEs that are ongoing with a toxicity of Grade 3 or 4, or have a relationship to study drug that is suspected (Reasonable Possibility) will be queried for resolution at study conclusion and at approximately 30 days after the last dose of study. New or updated information will be recorded on the originally completed SAE form in the Investigator's File, with all changes signed and dated by the Investigator.

#### *9.4.3 Regulatory reporting requirements for adverse events*

The Investigator must report immediately (within 24 hours from the knowledge) to the study Sponsor any SAE, occurred during the study whether related to the investigational product or not. The study Sponsor has the legal responsibility to promptly notify, as appropriate, both the local regulatory authority and other regulatory agencies about the safety of a product under clinical investigation. The study Sponsor will comply with the Italian regulatory requirements related to the reporting of SAEs to regulatory authorities and the Independent Ethics Committee (IEC). In particular, all the Suspected Unexpected Serious Adverse Reactions (SUSARs) that occur while on treatment and within 30 days since the last investigational drug administration, and that have a

[figure not shown]

suspected relationship to study's drug (Reasonable Possibility) will be notified with an urgency procedure to the local regulatory Agency (AIFA) and IEC with the following timelines:

- SUSARs that are considered life-threatening: notification within 7 days.
- SUSARs that are not considered life-threatening: notification within 15 days.

The notification with urgency procedure is not required for SAEs that are expected with the drugs used in the protocol, and for non-serious AEs, both expected and unexpected. For these events (expected SAEs and AEs), the CT will notify the local regulatory agency and IECs by an annual safety report.

## 9.5 Secondary and Exploratory endpoints

Dedicated blood samples will be collected at different time points (see APPENDIX 2: Timeline scheme) and processed at the biobank of the INMI.

### 9.5.1 SARS-CoV-2 Antibodies

The development of a specific humoral response will be monitored by measuring specific anti SARS-CoV-2 antibodies in the sera of patients collected at day 14 and 28 post randomization. Commercially available tests will be used to detect IgM specific for S antigen, IgG specific for the N and S antigens, and IgA specific for S antigen. Sera resulting reactive with the S antigen will be tested for the capacity of viral neutralization using standardized methods.

### 9.5.2 Molecular IFN-I signaling

Blood samples will be collected at T1 prior first treatment, during treatment (T3 prior second treatment) and post treatment (T14) and processed at the biobank of the INMI. Isolated PBMC will be aliquoted, submerged with RNA stabilization reagent and cryopreserved. For analysis, total RNA will be isolated and the transcriptional analysis of over 500 general immunology genes will be performed by means of Nanostring technology. Data analysis will determine the transcriptional modifications occurring during the course of IFN- $\beta$ 1a treatment as well as to identify molecular patterns potentially correlated with clinical outcome. Particular focus will be given to the ISG score reported to be differentially expressed among mild to severe COVID-19 (22). This exploratory analysis will be conducted by [name] and [name], having a relevant background on IFN signaling analysis (51,54)

[figure not shown]

### 9.5.3 Cellular Immune monitoring

Pre-(T1 prior treatment) and post-treatment (T3 and T14) blood samples will be monitored by MFC-based assays through different antibody panels in order to analyze frequency of major leukocyte subpopulations associated with naïve/memory, co-activation and co-inhibition markers; polyfunctional properties of T cell specific response against virus antigens will be evaluated after short term in vitro culture.

Stained samples will be acquired on a Beckman Coulter CytoFlex Cytometer and analyzed by CytExpert and/or Kaluza software as well as by advanced machine learning algorithms such as FlowSOM and CITRUS (Cytobank online platform). [name] and [name], co-investigators at ISS unit, have long lasting experience in MFC assays and immune-monitoring (52,55,56).

### 9.5.4 Systemic Inflammatory markers

Pre- (T1 prior treatment) and after-treatment (T14) blood samples will be collected from Treatment and control group to monitor the levels of soluble factors involved in inflammation (e.g., cytokines and chemokines) and endothelial cell adhesion molecules. At the selected time points, plasma will be isolated from peripheral blood and cryopreserved until analysis that will be simultaneously conducted by means of specific ELISA assays. Data will be integrated with the results of routine lab tests on coagulation factors and factors involved in COVID-19 pathogenesis (CRP, IL-6, TNF- $\alpha$ , Fibrinogen and D-Dimer).

## 10. Statistical Plan

The primary analysis will be carried out on the primary endpoint on the intention-to-treat (ITT) population defined as all patients randomized receiving at least one dose of treatment.

The percentage of patients undergoing disease progression defined on rate of progression of NEWS2 score lasting more than 5 days will be calculated in two arms (IFN- $\beta$ 1a + standard of care vs standard of care) of the trial. For persons who died, a conservative approach will be adopted and death will be considered an event. The effect of treatment will be estimated through a logistic regression model including a dummy variable for treatment. The effect of treatment will be estimated through multivariable logistic regression model by accounting for the following

[figure not shown]

covariates: age, gender, co-morbidities. Moreover, NEWS2 score at baseline and setting of recruitment will be also considered.

All primary and secondary analyses will be carried out both on ITT population and on per-protocol population. Per-protocol population includes all subjects who were included in the ITT population that received the treatment as defined in the protocol and who completed the study with no major protocol violations.

Kaplan-Meier survival analysis and Cox proportional hazards model will be used for time-to-event data. The following covariates will be included in the Cox model: age, gender, co-morbidities. Moreover, NEWS2 score at baseline and setting of recruitment will be also considered. For the secondary endpoint ICU-free days, a competing risk model will be adopted considering death a competing event, following the method proposed by Fine and Gray (57). Moreover, the median difference will be reported.

The longitudinal secondary endpoint measured on a continuous scale (the increase in SARS-CoV 2-Specific Binding Antibody Titers in IFN compared to control group) will be analysed using a Mixed effect Model for Repeat Measure (MMRM) to estimate the difference of mean change from baseline in SARS-CoV 2-Specific Binding Antibody Titers between IFN- $\beta$ 1a + standard of care and standard of care at day 28. In case of data sporadically missing during the course of trial we will assume they were Missing At Random (MAR). A sensitivity analysis will be carried out by conducting the statistical test after imputing missing, including the worst-case imputation. All missing data will be imputed within treatment groups defined by randomized treatment.

Safety endpoint will be compared by a chi-squared test for discrete variables, by means of analysis of variance (ANOVA) and covariance (ANCOVA) for continuous variables or by the non-parametric Mann-Whitney test when appropriate.

Confidence intervals (95%) will be reported for all outcomes and association measures (proportions, means, Odds Ratios and HRs).

For all statistical analyses (efficacy and safety), the level of statistical significance will be kept at 0.05 with two-sided p-values. Statistical analyses and related reports will be in full compliance with ICH E9 guidance ([https://www.ema.europa.eu/en/documents/scientific-guideline/ich-e-9-statistical-principles-clinical-trials-step-5\\_en.pdf](https://www.ema.europa.eu/en/documents/scientific-guideline/ich-e-9-statistical-principles-clinical-trials-step-5_en.pdf)).

[figure not shown]

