## 5.2 Secondary Objectives and Endpoints

The following table 1 contains the secondary objectives and endpoint of the study

| Objective                                                                                                                                                  | Endpoint                                                                                                           |
|------------------------------------------------------------------------------------------------------------------------------------------------------------|--------------------------------------------------------------------------------------------------------------------|
| 1) To assess the reduction in ICU admission in patients treated with IFN versus control group within 28 days of randomization                              | ICU-free days at 28 days (Day 1 through Day 28)                                                                    |
| 2) To assess the reduction in number of deaths in IFN compared to control group (day 28)                                                                   | All-cause mortality (Day 1 through Day 28)                                                                         |
| 3) To evaluate the increase in proportion of participants returning to negative SARS-CoV 2 RT-PCR in IFN-treated versus control group at Day 14 and Day 28 | Negative SARS-CoV 2 RT-PCR at day 14 post-randomization
Negative SARS-CoV 2 RT-PCR at day 28 post-randomization |

|                                                                                                                    |                                                                                      |
|--------------------------------------------------------------------------------------------------------------------|--------------------------------------------------------------------------------------|
| 4) To assess the increase in SARS-CoV 2-Specific Binding Antibody Titers in IFN compared to control group (day 28) | Change from Baseline in SARS-CoV 2-Specific Binding Antibody Titers at day 14 and 28 |
| 5) To assess the safety of IFN-treated patients versus control group                                               | Incidence of adverse events                                                          |

For secondary endpoints, more detailed descriptions follow:

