## 7.2. Criteria for eligibility

### 7.2.1 Inclusion criteria

- $\geq 65$  years of age at time of enrolment;
- Laboratory-confirmed SARS-CoV 2 infection as determined by PCR, in any specimen  $< 72$  hours prior to randomization;
- Subject (or legally authorized representative) provides written informed consent prior to initiation of any study procedures;
- Understands and agrees to comply with planned study procedures;
- Agrees to the collection of nasopharyngeal swabs and venous blood samples per protocol;
- Being symptomatic for less than 7 days before starting therapy;
- NEWS2 score  $\leq 2$

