### 8.2 Treatment arms

**Control arm.** No specific antiviral treatment besides standard of care.

[figure not shown]

**Treatment arm.** 11ug (3MIU) of IFN- $\beta$ 1a will be injected subcutaneously at day 1, 3, 7, and 10 in addition to standard of care. The drug solution, contained in a pre-filled cartridge, will be injected by means of the RebiSmart electronic injection device, as described in Appendix 6.

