### 9.4. Safety Criteria Evaluation

#### 9.4.1 Safety profile

Subjects participating in this trial who received at least one dose of the trial medication are considered to be included in the safety population (full analysis population). Safety population not include subjects who drop out prior to receiving any treatment. Data on safety profile, nature, incidence and severity of adverse events (AEs) and serious adverse events (SAEs) will be collected as detailed in both this section of the protocol and in the AE/SAE section of the CRF. Any reason for drug interruption, reduction and discontinuation will be collected. Toxicities will be graded using NCI Common Terminology Criteria for adverse Events (CTCAE) version 5. The investigator is responsible for detecting, documenting and reporting AEs and SAEs, according to the criteria defined in this protocol.

The safety profile of experimental drug (i.e., IFN- $\beta$ 1a, Rebif®) has been well established. Below are the very common and common adverse reactions as reported in the Summary of Product Characteristic 2010:

| Very common ( $\geq 1/10$ )                                                          | Common ( $\geq 1/100$ to $< 1/10$ )                             |
|--------------------------------------------------------------------------------------|-----------------------------------------------------------------|
| Neutropenia, lymphopenia, leukopenia, thrombocytopenia, anaemia                      | Diarrhoea, vomiting, nausea                                     |
| Asymptomatic transaminase increase                                                   | Severe elevations in transaminases                              |
| Headache                                                                             | Pruritus, rash, erythematous rash, maculopapular rash, alopecia |
| Injection site inflammation, injection site reaction, influenza-like symptoms | Myalgia, arthralgia                                             |
|                                                                                      | Depression, insomnia                                            |
|                                                                                      | Injection site pain, fatigue, rigors, fever                     |

[figure not shown]

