## 3. Approvvigionamento del farmaco e dell'iniettore

Per i soli pazienti rientranti nel braccio di trattamento, il giorno previsto per l'inizio del trattamento l'investigatore o un suo delegato deve presentarsi presso la Farmacia e richiedere una dose di farmaco e un dispositivo per l'autoiniezione del farmaco utilizzando il modulo Allegato 1. Il modulo originale deve essere conservato dalla Farmacia fino al ritorno del dispositivo per l'autoiniezione, dopodiché il modulo viene conservato nella cartella clinica del paziente.

Per i soli pazienti non ospedalizzati, l'investigatore dovrà accertarsi di essere inoltre in possesso di:

- Sei aghi Serofine 29G, 30G o 31G;
- Un contenitore per rifiuti sanitari pericolosi a rischio infettivo (taglienti e pungenti);
- Un diario clinico del paziente (fornito dal Promotore);
- Uno sfingomanometro digitale, un termometro e un saturimetro per la misurazione dei parametri vitali (fornito dal Promotore);
- Un manuale d'uso del Rebismart (da usare in caso di necessità);
- Salviettine o tamponcini imbevuti di alcol o batuffoli di ovatta e alcol per frizione;
- Cerotti (classici e a rochetto)

[figure not shown]**MODALITÀ DI APPROVVIGIONAMENTO E SOMMINISTRAZIONE DEL FARMACO  
REBIF TRAMITE INIETTORE REBISMART****4. Attivazione e settaggio dell'iniettore Rebismart e caricamento cartuccia Rebif****4.1 Inserimento pile**

In caso il dispositivo abbia le batterie scariche, prelevare il dispositivo Rebismart dalla scatola contenitore e indossare il cinturino per impedire che il dispositivo possa cadere accidentalmente. Svitare la vite del coperchio dell'alloggiamento pile con un cacciavite e far scivolare verticalmente il coperchio. Inserire 4 pile al litio nuove. Verificare che siano orientate come mostrato sul dispositivo e stringere la vite del coperchio dell'alloggiamento delle pile per chiuderlo. Una sequenza illustrata della attività da eseguire è riportata nell'allegato 2.

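### The set called ITT requires a dose, a condition that can exclude only IFN patients after open randomisation, and the safety set, read literally, contains no controls

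*Protocol*

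**What the plan says.** Section 10 places the primary analysis on an ITT "population defined as all patients randomized receiving at least one dose of treatment". The per-protocol set is a subset of it, and all primary and secondary analyses are to be run on both.

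The control arm in section 8.2 is described as "No specific antiviral treatment besides standard of care"; there is no placebo. Appendix 2 schedules interferon for the second arm only, and the drug procedure in Appendix 6 opens its supply section with "Per i soli pazienti rientranti nel braccio di trattamento" (only for patients in the treatment arm). Section 9.2 states that the trial is open-label and that patients learn their arm after randomisation.

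Section 9.4.1 defines the safety set in different words: "Subjects participating in this trial who received at least one dose of the trial medication are considered to be included in the safety population". It adds: "Safety population not include subjects who drop out prior to receiving any treatment". Yet secondary objective 5 in section 5.2 is "To assess the safety of IFN-treated patients versus control group", section 10 plans between-arm tests of the safety endpoints, and Appendix 2 records adverse events in both arms from T1 to T28.

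No section says how a dose condition applies to a control patient.

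**The concern.** An ITT set includes patients because they were randomised. This one also requires something that happens after randomisation and can happen in only one arm. An IFN patient who deteriorates, refuses or withdraws between randomisation and the first injection leaves the primary set. A control with the same course stays and is counted.

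The protocol leaves room for this. Appendix 4 records randomisation on the screening page and the first dose at T1, so there is a gap, of unstated length. The patient knows the arm during that gap, so a decision not to start can depend on it. Section 8.5 stops IFN in progressing patients who need oxygen but keeps them in follow-up. A patient who reached that state before T1 might never be dosed, and would be lost from the analysis although the outcome was observed.

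At stake is whether the primary comparison is the randomised one. For safety, the planned comparison lacks a rule that admits the comparator.

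**Working it through.** **Step 1: the plan's own figure.** Inputs from section 5.4: progression 0.15 (IFN) and 0.50 (control), two-sided 5%, 80% power, 2:1. The Fleiss formula without continuity correction, for the control arm with k = 2, is

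n = [z(0.975)·√(p̄(1−p̄)(1+1/k)) + z(0.80)·√(p_C(1−p_C) + p_I(1−p_I)/k)]² / (p_C − p_I)²

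with p̄ = (0.50 + 2×0.15)/3 = 0.267. The numerator is (1.062 + 0.471)² = 2.35 and the denominator is 0.35² = 0.1225. So n = 19.2, rounded up to 20, which gives 40 + 20 = 60. The stated figure is reproduced; power at 40 and 20 is 81.6%. The calculation therefore counts every randomised patient.

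**Step 2: whom the conditions admit.**

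| Set | Condition | IFN arm | Control arm |
|---|---|---|---|
| ITT, section 10 | a dose of treatment | 40 minus those undosed | 20, if standard of care counts as treatment |
| Safety, section 9.4.1 | a dose of the trial medication | 40 minus those undosed | none, read literally |

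**Step 3: effect on power.** The number undosed is not given; 0 to 8 is assumed. With 0, 1, 2, 4, 6 or 8 IFN patients removed and 20 controls kept, power is 81.6%, 81.2%, 80.8%, 79.9%, 78.8% or 77.7%. The loss is small, so power is not the issue.

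**Step 4: effect on the type I error.** Assume a true 50% in both arms, 40 versus 20, and an uncorrected two-sided 5% chi-square test. A share e of IFN progressors and a share f of IFN non-progressors go undosed and are dropped. The expected IFN rate is then 0.5(1−e) / [0.5(1−e) + 0.5(1−f)]. The chance of a significant result favouring IFN comes from exact enumeration of the binomial outcomes.

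| Assumed loss in the IFN arm | IFN rate | False result favouring IFN |
|---|---|---|
| none | 50.0% | 2.7% |
| 10% of progressors only | 0.45/0.95 = 47.4% | 4.0% |
| 20% of progressors only | 0.40/0.90 = 44.4% | 6.2% |
| 10% or 20% of all IFN patients | 50.0% | 2.6% |
| 10% of non-progressors only | 0.50/0.95 = 52.6% | 1.6% |

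**Step 5: one patient.** For a 2×2 table, χ² = N(ad − bc)² / (product of the four margins). With controls at 10/20:

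- IFN 10/40: 60×(10×10 − 30×10)² / (40×20×20×40) = 3.75, p = 0.053.
- IFN 9/39, one progressor dropped: 59×(9×10 − 30×10)² / (39×20×19×40) = 4.39, p = 0.036.
- IFN 8/38, two dropped: 58×(8×10 − 30×10)² / (38×20×18×40) = 5.13, p = 0.024.

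**The case against.** **The primary set obviously keeps its controls.** This stands. A reader might infer from the dose condition that none of the 20 controls qualifies for ITT. The documents do not support that. Section 10 says treatment, not trial medication; sections 6, 8.2 and 9.1 use the word for both arms; and section 10 goes straight on to compare two arms. But keeping the controls is what makes the condition one-sided, because no control dose is defined that a control could fail to receive.

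**A bias towards IFN is not shown.** This also stands. A reader might infer that the exclusions must favour IFN. The protocol says nothing about the prognosis of undosed patients. Those who feel well may decline injections, which would work against IFN, and loss unrelated to outcome causes no inflation (step 4).

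**The assumed loss may be too high.** Entrants have a NEWS2 score of at most 2 and the gap before T1 may be short. Losing 10% to 20% of about 20 IFN progressors means 2 to 4 patients; at 5% the false-positive rate is only 3.2%. The test used here is also not the planned adjusted logistic model. Both are fair limits on the figures. Neither makes the definition ITT.

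**Control safety data will exist.** Adverse events are recorded in both arms, so what is missing is the rule that admits controls to the set, not the comparator.

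**Symptom duration.** Section 7.2.1 asks for "Being symptomatic for less than 7 days before starting therapy", and a reader might see the same one-arm fault there. It is an eligibility check made at screening before allocation, and no section removes a patient for it after randomisation. It is not part of this point.

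**Conclusion.** The definition in section 10 is not ITT. It conditions the primary set on an event after randomisation that can fail only in the IFN arm, with the allocation known. The per-protocol set is nested in it and cannot repair this. The direction of the bias is open. Under a 50% null, the chance of a false result favouring IFN lies between 1.6% and 6.2% across the scenarios tried, against 2.7% with no exclusions. Those scenarios rest on assumed shares of undosed patients and on assumptions about who they are. With 40 and 20 patients, a single exclusion can carry the result across 0.05.

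The safety definition in section 9.4.1 is a separate fault. Taken literally it excludes every control, contrary to secondary objective 5 and to the tests planned in section 10.

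The sample size is not affected: all randomised patients are the 60 that section 5.4 counts. Both definitions should be corrected before outcomes are compared by arm.

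**What to change.** - **Section 10:** define ITT as all randomised patients, analysed in the arm to which they were allocated, whether or not they were dosed.
- **Section 9.4.1:** define the safety set as IFN patients who received at least one dose plus all randomised controls, observed from T1 in both arms.

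The cost is wording in two sections, with no extra patients, visits or data. A few undosed IFN patients in the primary set may dilute the effect slightly. The per-protocol analysis already planned can show the result in patients treated as intended, with the usual caution that it is not a randomised comparison.

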#### 5.4 Statistical hypothesis

The trial power has been calculated by the ISS group. The study was powered to independently assess a potential benefit of IFN- $\beta$ 1a compared with control arm (no specific antiviral treatment besides standard of care) on rate of progression of NEWS2 score lasting more than 5 days.

Sample size was calculated according to the primary endpoint of the study. In particular, the sample size calculation is based on the assumptions of an at least 35% difference in the percentage of patients undergoing disease progression between IFN- $\beta$ 1a and control arm. A sample size of 60 patients total (40 in the IFN- $\beta$ 1a-treated arm and 20 in the control arm, according to a 2:1 randomization ratio) will be needed to provide 80% power at significance level of 5% to detect the difference of patients undergoing disease progression between a group 1 proportion of 0.15 (IFN- $\beta$ 1a + standard of care) and a group 2 proportion of 0.50 (standard of care).

[figure not shown]

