#### 8.5 Safety monitoring and individual stopping rules

Any sign or symptom associated to drug adverse events will be daily reported.

Progressing patients which are in need of oxygen support will be maintained in the trial for follow up purposes, but treatment will be discontinued (Appendix 1). Progressing patients will receive standard of care or additional treatment at the physician discretion.

Another stopping rule includes drug related adverse events grade  $\geq 3$  according to Common Terminology Criteria for Adverse Events (CTCAE) version 5.0.

[figure not shown]

For progressing patients, we will record the admission to the intensive care unit, days in ICU, and the disease outcome (either survivor or non-survivors) by using the Regional surveillance systems. Patients are free to withdraw from participation in the study at any time upon request, without any consequence. Patients should be listed as having withdrawn consent only when they no longer wish to participate in the study and no longer authorize the Investigators to make efforts to continue to obtain their outcome data. Every effort should be made to encourage patients to remain in the study for the duration of their planned outcome assessments. Patients should be educated on the continued scientific importance of their data, even if they discontinue the study. In the case of a patients becoming lost to follow-up, attempts to contact the patient should be made and documented in the patient's medical records.

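### Sections 5.1.1, 5.4 and 10 define the primary event differently, so patients who reach ICU or ventilation and recover quickly, or who worsen after T23, have no settled classification

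*Protocol*

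**What the plan says.** The protocol describes the primary event, or the patients who ought to have it, in four places.

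- **Section 5.1.1** asks for NEWS2 progression over 5 days or more. Its last sentence also accepts any other clinical sign that clearly shows worsening. No sign is named and no duration is attached.
- **Section 5.4** bases the sample size on NEWS2 progression of more than 5 days.
- **Section 10** analyses "The percentage of patients undergoing disease progression defined on rate of progression of NEWS2 score lasting more than 5 days". It then adds one automatic event: "For persons who died, a conservative approach will be adopted and death will be considered an event". Oxygen, ICU admission and ventilation are not mentioned.
- **Section 8.5** uses the word progressing for patients whom section 10 may not count: "Progressing patients which are in need of oxygen support will be maintained in the trial for follow up purposes, but treatment will be discontinued". It continues: "Progressing patients will receive standard of care or additional treatment at the physician discretion". On data capture it says: "For progressing patients, we will record the admission to the intensive care unit, days in ICU, and the disease outcome".

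Section 9.2 makes the trial open-label. Appendix 2 schedules NEWS2 every day from T1 to T28 in both arms.

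**The concern.** The trial aims to reduce progression towards severe COVID-19. A patient who is admitted to ICU or ventilated has plainly reached that state. Yet the analysis section, taken at its word, needs a NEWS2 run of more than 5 days or a death before it counts an event. A patient who deteriorates, receives additional treatment and improves within 5 days could enter the analysis as a success. The same holds for a patient who deteriorates too late in the 28-day window for the run to be completed.

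Section 5.1.1 could give the opposite answer for the same patient. With the sections as they stand, someone who knows the allocation may have to choose between two readings after the clinical course is known. In a trial of 60 patients, a few such choices affect the primary comparison.

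**Working it through.** **1. The plan's own figures.** Inputs from section 5.4: 0.15 (IFN) against 0.50 (control), 40 and 20 patients, "80% power at significance level of 5" per cent. Section 10 makes the test two-sided: "the level of statistical significance will be kept at 0.05 with two-sided p-values".

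Pooled proportion: (40 × 0.15 + 20 × 0.50) / 60 = 16/60 = 0.267.

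Control patients needed (Fleiss, no continuity correction, ratio r = 2):

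n = [1.96 × √((1 + 1/r) × 0.267 × 0.733) + 0.842 × √(0.50 × 0.50 + 0.15 × 0.85 / r)]² / 0.35²
= (1.062 + 0.471)² / 0.1225 = 19.2, rounded up to 20.

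This gives 20 + 40 = 60, as stated. With continuity correction the result is 24 + 48 = 72, which also matches the table in section 5.4.

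Power with 40 and 20:
- standard error under no difference: √(0.267 × 0.733 × (1/40 + 1/20)) = 0.1211
- standard error under the planned rates: √(0.15 × 0.85/40 + 0.50 × 0.50/20) = 0.1252
- (0.35 − 1.96 × 0.1211) / 0.1252 = 0.90, so power is about 81.6%.

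The sample size is not in question.

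**2. The same patient under each section.**

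| Course (patient survives) | 5.1.1 | 5.4 and 10 | 8.5 |
|---|---|---|---|
| ICU or ventilation, NEWS2 back within 5 days | Event if read as another clear sign | Non-event | Progressing, if oxygen is needed |
| NEWS2 worse on exactly 5 days | Event | Non-event | Not addressed |
| Worse from T24 to T28 | Event (5 daily scores) | Non-event | Not addressed |
| Worse from T25 or later | Event only as another clear sign | Non-event | Not addressed |
| New oxygen, NEWS2 back within 5 days | Event if read as another clear sign | Non-event | Progressing |

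The T23 limit counts daily scores. T23 to T28 is 28 − 23 + 1 = 6 scores, the shortest run longer than 5. T24 to T28 is 5 scores and does not qualify. If elapsed days were meant, the limit would fall one day earlier.

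**3. What one classification is worth.** Expected events at the planned rates are 0.50 × 20 = 10 control and 0.15 × 40 = 6 IFN. One control patient is 1/20 = 5 points and one IFN patient is 1/40 = 2.5 points. For illustration, take two patients who change status:

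- two control events become non-events: 8/20 = 40% against 15%, difference 25 points
- two control non-events become events: 12/20 = 60% against 15%, difference 45 points
- two IFN events become non-events: 50% against 4/40 = 10%, difference 40 points
- two IFN non-events become events: 50% against 8/40 = 20%, difference 30 points.

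The planned difference is 35 points. The choice of two patients is only an illustration. Nothing in the protocol says how many patients would be affected, or in which arm.

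**The case against.** The strongest reply is that section 5.1.1 carries the heading of the primary endpoint and that its closing sentence already covers these patients. ICU care or ventilation is the plainest example of clear clinical worsening. Section 5.4 is sample-size text, and section 10 refers back to the primary endpoint without saying that nothing else counts. This stands in part. A reader might infer from section 10 that such patients are definitely non-progressors, but the documents do not go that far. They leave the status open, because the clause names no sign and sections 5.4 and 10 do not repeat it.

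Three other strong readings are also unsupported.

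- **That progressing patients drop out of daily scoring.** Section 8.5 keeps them in follow-up and Appendix 2 schedules NEWS2 daily to T28.
- **That the duration rule costs a calculable amount of power.** Section 5.4 ties the rates of 0.50 and 0.15 to the event lasting more than 5 days. Reducing them again for events missed by that rule would subtract the same thing twice, using shares that the protocol does not give.
- **That the bias must run against IFN.** Unequal classification could favour either arm.

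It is also fair to say that requiring sustained worsening is a legitimate design choice, and that ICU-free days and mortality are secondary endpoints, so severe courses are not lost from the trial. Those points defend having a duration rule. They do not settle which of the two stated rules applies.

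**Conclusion.** The point holds as an inconsistency in the definition of the primary event. Sections 5.1.1 and 10 give different durations, only one of them has an open clause for other worsening, and section 8.5 uses progressing for patients whom section 10 may not count. The protocol itself fixes these definitions, so this is not detail left for a later analysis plan.

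The patients affected are survivors with a short severe episode, a run of exactly 5 days, or an onset after T23 (counting daily scores). How many there will be cannot be derived from the documents. What can be stated is the leverage: 5 points per control patient and 2.5 per IFN patient, on about 16 expected events, in either direction. Open-label care, with additional treatment at the physician's discretion, means that equal effects in the two arms cannot be assumed. The stated sample size and power are reproduced and are not challenged.

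**What to change.** Put one identical event definition in sections 5.1.1, 5.4 and 10, with a single duration wording. In it:

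- Extend the rule for death, so that ICU admission or mechanical ventilation between Day 1 and Day 28 counts as progression whatever its duration.
- State explicitly how new supplemental oxygen counts.
- State how a worsening still present at T28 counts.
- Report the definition based on NEWS2 duration alone as a sensitivity analysis.

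Add an explicit air/oxygen entry to the NEWS2 section of the eCRF. The fields listed in Appendix 4 include SpO2 but not oxygen use, although Table 2 scores it. The same entry can record ventilation, which those fields also omit.

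The cost is a protocol amendment and one eCRF field; ICU admission and ICU days are already to be recorded. The oxygen decision carries a real trade-off. If any oxygen start counts, a decision by unblinded clinicians enters the primary endpoint, and brief precautionary use becomes an event. If it does not count, the text should say so, because section 8.5 calls these patients progressing. The change concerns only what is counted as an event; it does not touch the treatment or stopping rules.
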